## Methods

### Overview of Project Research Design

This is a multicenter prospective longitudinal cohort study of patients newly prescribed with medicinal cannabis in Australia by authorized prescribers and under the SAS. The study is registered in the Australian New Zealand Clinical Trials Registry (ACTRN12621000063819).

### Study Arrangements

To be eligible to participate in the study, participants must have already been identified as eligible to receive a medicinal cannabis product from an authorized prescriber or under the SAS category B pathway, with approval given by the Australian TGA. This means that a suitable health practitioner has seen and assessed their patient, adhering to relevant standards of good medical practice, and successfully applied to the TGA for access to the particular medicinal cannabis product for the patient. Little Green Pharma Ltd (LGP) is responsible for the manufacture and quality of the products following the TGA guidelines. The prescriber is responsible for the prescription of the product for the patient and seeking TGA approval either as an authorized prescriber or under the SAS-B scheme, including the patient’s informed consent for the product.

The University of Sydney researchers are responsible for the design of the cohort study and the data collection and analysis, as outlined in this protocol.

LGP is responsible for arrangements for delivery of the product, any subsidization arrangements, and the arrangements entered into with the participating sites and the physicians at these sites.

The prescriber is responsible for identifying the patients suitable for the study and obtaining consent to email them an invitation to participate in the study.

### Eligibility

The inclusion and exclusion criteria are provided in Textbox 1.

Inclusion and exclusion criteria.
**Inclusion criteria**
Patient is an adult (aged ≥18 years).Patient has been identified as eligible to receive medicinal cannabis by a Therapeutic Goods Administration–approved authorized prescriber or through the Special Access Scheme (or equivalent in other countries and jurisdictions) and the physician has sought and obtained Therapeutic Goods Administration approval for the Little Green Pharma Ltd product for their patient.Patient is able to read and understand English.Patient is able to provide informed consent.Patient has not started any prescribed medicinal cannabis therapy in the last 4 weeks or started prescribed Little Green Pharma Ltd medicinal cannabis therapy within the last 2 days (we expect no therapeutic benefit within 2 days) and did not receive any prescribed medicinal cannabis therapy in the last 4 weeks.Patient has a life expectancy of >3 months.

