#### Patient Consent and Demographics

Patients who provide email addresses will receive an email with a link to the patient consent and demographic form corresponding to their study record ID. Patient consent and demographic questions include the following: consent to participate (or opt out), reasons for declining study participation (if applicable), ethnicity and cultural background, education, living arrangements, marital status, height, weight, gender identity, work status, access to health services, any medication other than medicinal cannabis taken during the last 4 weeks for health indication, and previous history of cannabis use.

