#### PRO Assessment Time Points

Prospective assessment of newly prescribed patients before and after treatment is required to assess changes in PROs over time. PROs will be completed at baseline before starting medicinal cannabis, at 2-3 weeks after starting medicinal cannabis (end of titration period), and then at 1, 2, 3, 5, 7, 9, and 12 months after the titration period.

The acceptable PRO assessment time windows are indicated in Table 1.

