#### Statistical Considerations

A comprehensive PRO-specific statistical analysis plan will be produced by the study statistician. The key considerations include the following:

PRO questionnaire responses will be scored into PRO scales for outcome analysis according to standard scoring algorithms provided by the questionnaire developers and custodians.Rates and reasons for missed PRO assessments will be summarized to assess likely missing data mechanisms against missing data assumptions of statistical modeling.For each PRO, all participants with a score for that PRO at baseline and at least one time point after starting medicinal cannabis will be analyzed.Linear mixed models will be used to compare groups in their PRO scores, adjusted for their PRO levels at baseline and with additional covariates such as duration of pain, previous cannabis use, use of other medications, and overall and prespecified subgroups.If the scores are highly skewed, a suitable transformation will be sought to achieve normality.As there are several PRO scales and time points and correlation among them is anticipated, statistical significance levels will be adjusted using an appropriate method [82].The clinical significance of differences in the PRO questionnaires will be interpreted using existing guidelines (eg, QLQ-C30) [83], maintaining the overall type 1 error at 5% or less.

Missing items within the PRO questionnaires are not expected. This is because of the web-based administration platform alerting participants of missed items and the requirement to complete those items before progressing to the next page. Only those participants who complete at least 2 questionnaires (baseline and one other) will be included in the analysis. Single missed assessments will be imputed using the last value carried forward technique, that is, no change from that individual’s last assessment. Pattern mixture models will be used to impute scores for missed assessments based on recorded reasons [84].

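### As worded, the prior-treatment criterion either admits patients already established on prescribed cannabis or cancels its own 2-day allowance; neither reading fits a newly prescribed cohort

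*Protocol article*

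**What the plan says.** In the Protocol article, Eligibility (Textbox 1), the prior-treatment criterion is one sentence holding three conditions. It opens "Patient has not started any prescribed medicinal cannabis therapy in the last 4 weeks or started prescribed Little Green Pharma Ltd medicinal cannabis therapy", continues "within the last 2 days (we expect no therapeutic benefit within 2 days", and closes "and did not receive any prescribed medicinal cannabis therapy in the last 4 weeks".

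Two other sections describe the intended cohort. Overview of Project Research Design speaks of "patients newly prescribed with medicinal cannabis in Australia by authorized prescribers and under the SAS". PRO Assessment Time Points says that "PROs will be completed at baseline before starting medicinal cannabis".

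Earlier use is recorded. Under Registration and Clinical Data, the site enters the date and dose of any cannabis prescribed before. Patient Consent and Demographics asks the patient for "previous history of cannabis use". Statistical Considerations lists "additional covariates such as duration of pain, previous cannabis use, use of other medications" for the linear mixed models.

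**The concern.** The first condition is about starting and the last is about receiving. These differ for anyone who began treatment more than 4 weeks ago and is still taking it. The conditions are also joined by an or and an and with nothing to show which binds first, so who is eligible depends on how a site groups them.

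The study has no control group. The primary objective is the change from baseline to 3 months, and the patient's own baseline is the only reference. A patient already on prescribed cannabis at baseline does not supply a before-starting value. The Patients' Global Impression of Change, which is anchored at the start of cannabis treatment, would also refer to an earlier date for that patient. The opposite error, refusing someone who began the study product the day before, defeats an allowance that the protocol deliberately wrote in.

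**Working it through.** **Inputs.** All three come from the inclusion criteria in Textbox 1.

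- A: no prescribed cannabis was started in the last 4 weeks.
- B: the study product was started within the last 2 days.
- C: no prescribed cannabis was received in the last 4 weeks. No exception is stated.

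**Two groupings, applied to typical patients.**

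| Patient | A | B | C | A or (B and C) | (A or B) and C |
|---|---|---|---|---|---|
| Never prescribed cannabis | yes | no | yes | eligible | eligible |
| Prescribed cannabis stopped more than 4 weeks ago | yes | no | yes | eligible | eligible |
| Another prescribed product begun more than 4 weeks ago, still taken | yes | no | no | **eligible** | not eligible |
| Another prescribed product begun 2 weeks ago | no | no | no | not eligible | not eligible |
| Study product begun yesterday, nothing else; C taken literally | no | yes | no | **not eligible** | **not eligible** |
| Same patient; C taken to leave out the study product | no | yes | yes | eligible | eligible |

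**Reading the table.**

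1. Under A or (B and C), the established user in row 3 is admitted, because only A has to be met.
2. Under (A or B) and C, that patient is excluded. But the patient in row 5 has received prescribed cannabis within 4 weeks and fails C, so B never makes anyone eligible.
3. Taken literally, C also voids the allowance under the first grouping. That grouping then has both faults.
4. One combination keeps the allowance and excludes established users: the second grouping, with C understood to leave out the study product begun within 2 days. The sentence does not say this.

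**Comparison with the other sections.** Row 3 conflicts with the newly prescribed description and with a baseline before starting. Row 5 conflicts with the allowance in the criterion itself. The allowance is in turn an unmentioned exception to the baseline timing in PRO Assessment Time Points.

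**Size.** The documents give no share of established users, so the effect on the primary result cannot be computed. The following is an illustration only. The planned 2142 is reproduced by a one-sample test of a standardised change of 0.1 at two-sided 1% and 95% power: 1785 by noncentral t, and 1785 × 1.20 = 2142. Now assume that a share f of those analysed has zero change, that the others change by 0.1, and that the SD is unchanged. Power is then about Φ(0.1 × (1 − f) × √1785 − 2.576).

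| Assumed f | Mean change | Power, 1785 analysed |
|---|---|---|
| 0% | 0.100 | 95% |
| 5% | 0.095 | 92% |
| 10% | 0.090 | 89% |
| 20% | 0.080 | 79% |
| 30% | 0.070 | 65% |

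If 20% of 2142 are lost, 1713 remain, and the figures become 94%, 91%, 87%, 77% and 62.5%. Nothing in the article supports any particular f or the assumption of zero change.

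**The case against.** The strongest reply is that the intent is clear. The article describes newly prescribed patients, places baseline before treatment, and ends the criterion with a no-receipt condition. A sensible reader would take that condition to apply to everyone and to leave out the start just allowed in the same sentence. On that reading the population is the intended one. Sites are also trained in screening, and dates of earlier prescriptions are recorded. All of this stands: admission of established users is a risk of one literal reading, not the evident plan, and the article does not show that any were enrolled. It does not remove the need for a change, because the operative rule should say what the other sections say.

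A reader might also infer three stronger points that the article does not support.

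- *The primary change is diluted and power is lost.* This needs a share of established users and their expected change, and neither is given. The 0.1 is the smallest threshold used for one QLQ-C30 domain, not the expected effect.
- *Non-prescribed cannabis is ignored.* The criterion does not limit it, but cannabis history is collected and previous use is a named covariate. Admitting such patients fits the stated aim of a broad real-world sample.
- *Previous use is adjusted for only as a main effect, which is inadequate.* The article does not say how the covariate enters the model, and a use-by-time term is properly left to the statistical analysis plan.

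**Conclusion.** The criterion is wrong as written. One literal grouping lets in patients established on prescribed cannabis, and the other cancels the 2-day allowance. Neither agrees with the cohort and the baseline described elsewhere in the article.

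This is more than clerical, because the sentence decides whether the baseline is a pre-treatment value, and baseline is the sole comparator. By 4 June 2021, 69 physicians had screened 1095 patients, which leaves room for different readings across sites. It is less than a demonstrated bias. The harm to the primary change arises under one grouping only, and its size is unknown. The conclusion rests on the wording alone and on no assumed share of patients.

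**What to change.** Reconcile the criterion with Overview of Project Research Design and PRO Assessment Time Points. The 4-week condition should refer to receipt of prescribed cannabis and apply to every patient. A start of the study product within 2 days should be its only stated exception, and the section on time points should mention that exception.

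For patients already enrolled, use the recorded date of previously prescribed cannabis to flag those who were on it in the 4 weeks before baseline. Report the primary change from baseline to 3 months with and without them. The article does not say whether the recorded date is a start or a last-use date. If it is only a start date, a query to the site would settle the flag, since sites keep the list of study ID numbers.

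The cost is one reworded sentence, one cross-reference, some possible site queries and one sensitivity table, in which the analysed set may be slightly smaller. No enrolled patient has to leave the main analysis.

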**Exclusion criteria**
Patient is unconscious or confused.Patient has cognitive impairment (eg, advanced Alzheimer disease).Patient is pregnant or breastfeeding.Patient is unable to read and write in English.Patient is denied access to medicinal cannabis under the relevant Special Access Scheme for their country of registration.

### Sample Size

#### Sample Size Considerations

Our aim is to recruit a large, broad, and representative sample of medicinal cannabis users. Therefore, we will invite every eligible patient treated at each participating center during a 12-month recruitment period. This large real-world cohort will enable several important analyses exploring differences in PROs between disease groups commonly treated with medicinal cannabis, as discussed in the *Objectives* section.

#### Minimum Sample Required for Primary Objective (Change Over Time)

Following the guidelines [51] for the European Organization for the Research and Treatment of Cancer Quality of Life Questionnaire-30 (EORTC QLQ-C30) [52] and allowing for a 20% loss to follow up, a baseline sample size of 2142 is required with a minimum follow-up of 3 months. This sample size provides 95% power to detect the smallest effect size threshold of 0.1 for the insomnia domain of the QLQ-C30, using a 2-tailed significance level of 1% [53].

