**Methods:**

Adult patients newly prescribed medicinal cannabis oil by authorized prescribers and under the Special Access Schemes across Australia will be screened for eligibility and invited to participate. A sample size of 2142 is required, with a 3-month follow-up. All participants will complete the EuroQol 5-Dimension; European Organization for Research and Treatment of Cancer Quality of Life Questionnaire-30; Depression, Anxiety, and Stress Scale-21; Patients’ Global Impression of Change; Patient-Reported Outcomes Measurement Information System (PROMIS) Short Form (SF) version 1.0: Sleep Disturbance 8b; and PROMIS SF Fatigue 13a questionnaires. Patients with chronic pain conditions will also complete the PROMIS SF version 1.0: Pain Intensity 3a and PROMIS SF version 1.0: Pain Interference 8a. Patients with movement disorders will also complete Quality of Life in Neurological Disorders (Neuro-QoL) SF version 1.0: Upper Extremity Function (Fine Motor and Activities of Daily Living) and if chorea is indicated, the Neuro-QoL SF version 2.0: Huntington’s Disease health-related Quality of LIFE-Chorea 6a. All questionnaires will be administered at baseline, 2 weeks (titration), monthly up to 3 months, and then every 2 months up to 1 year.

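### The baseline sample of 2142 matches a 20% loss allowance made by multiplying by 1.2 instead of dividing by 0.8, so it does not give the stated 95% power after 20% loss

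*Protocol article*

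**What the plan says.** The only sample size justification is in the protocol article under Minimum Sample Required for Primary Objective (Change Over Time). It says that, "allowing for a 20% loss to follow up, a baseline sample size of 2142 is required with a minimum follow-up of 3 months", and continues: "This sample size provides 95% power to detect the smallest effect size threshold of 0.1 for the insomnia domain of the QLQ-C30", at a two-tailed significance level of 1%. The abstract (Methods) repeats the figure: "A sample size of 2142 is required, with a 3-month follow-up".

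The Primary Objective is change from baseline to 3 months in one cohort, so the calculation concerns a within-patient comparison. The abstract (Results) reports 833 participants with completed baseline questionnaires as 39% of the target. Since 833/2142 = 38.9%, this confirms that 2142 counts people at baseline, before any loss.

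The article does not print the number needed with 3-month data, the test assumed, or the formula used for the loss allowance.

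**The concern.** If a fraction of participants will be lost, the number needed for analysis has to be divided by the fraction that remains. Multiplying by one plus the loss rate gives too small a number, because the loss is then taken from the enlarged sample. A 20% loss calls for a factor of 1/0.8 = 1.25, not 1.2.

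The printed 2142 looked like the product of the smaller factor. If so, the baseline number, the loss rate and the power in that section do not agree with each other. The figure is the only planning number for the primary objective. It is also repeated in the abstract as the required sample, serves as the denominator for reported recruitment progress, and underlies the stated end of recruitment.

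**Working it through.** **Inputs, all from the sample size section unless noted**

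- Effect size 0.1: "smallest effect size threshold of 0.1 for the insomnia domain of the QLQ-C30". No SD or correlation is given, so 0.1 is taken as mean change divided by the SD of change.
- Two-sided alpha 0.01.
- Power 95%.
- Loss: "allowing for a 20% loss to follow up".
- Design: paired change from baseline to 3 months in a single cohort (Primary Objective).
- Printed result: "a baseline sample size of 2142 is required with a minimum follow-up of 3 months".

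**Step 1. Number needed with both assessments.** The normal approximation is n = ((z₀.₉₉₅ + z₀.₉₅)/d)² = ((2.5758 + 1.6449)/0.1)² = 1781.4, so 1782. The exact paired t-test (non-central t) gives n = 1785: power is 0.95003 at 1785 and 0.94991 at 1784.

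**Step 2. Reproduce the printed figure.**

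| Number needed for analysis | × 1.2 | ÷ 0.8 (rounded up) |
|---|---|---|
| 1785 (exact t) | 2142.0 | 2231.25 → 2232 |
| 1782 (normal) | 2138.4 → 2139 | 2227.5 → 2228 |

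The exact t result multiplied by 1.2 gives 2142 to the unit, with every input as printed and nothing left to tune. Division by 0.8 misses by 2232 − 2142 = 90, about 4%.

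**Step 3. Check that no other standard calculation gives 2142 with the correct division.**

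- One-sided 1%: 1580 needed, 1975 after ÷ 0.8.
- Two-sided 5%: 1302 needed, 1628 after ÷ 0.8.
- 90% power at two-sided 1%: 1492 needed, 1865 after ÷ 0.8.
- Wilcoxon efficiency adjustment (3/π): 1869 needed, 2337 after ÷ 0.8.
- Two-sample formula: 3563 per group, which does not fit the design and is already larger than 2142.

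None reaches 2142.

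**Step 4. Check which sample the 95% describes.** With all 2142 analysed, power is 98.0%. The 95% therefore belongs to 1785 completers, and 2142 is that number after inflation.

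**Step 5. What 2142 delivers.**

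- After 20% loss: 2142 × 0.8 = 1713.6, so about 1713 completers, which is 1785 − 1713 = 72 short.
- Power at 1713: 94.05% (exact t) or 94.1% (normal).
- Effect detectable with 95% power at 1713: 4.2207/√1713 = 0.102.
- Loss that 2142 can absorb at 95% power: 1 − 1785/2142 = 16.7%.

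**The case against.** The arithmetic itself is hard to dispute. The case on the other side concerns certainty and weight.

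- **The 1.2 multiplier is not printed.** This is true; it is inferred. The section also does not say which SD standardises the 0.1. If it were the baseline SD, then n = 1781.4 × 2(1 − ρ), where ρ is the correlation between the two assessments. With ρ = 0.52 this gives 1710, and 1710/0.8 is about 2138, close to the printed figure. The baseline number after correct division would be about 3117 at ρ = 0.3, 2672 at ρ = 0.4, 2227 at ρ = 0.5 and 1781 at ρ = 0.6. But the article states no correlation, and this route only comes near 2142, whereas the printed inputs with × 1.2 meet it exactly. What stands is that the assumption has to be named.
- **Completer power is not the power of the planned analysis.** The analysis sections specify linear mixed models, keep anyone with a baseline and at least one later score, and impute missed assessments. Table 1 has three assessments between baseline and the 3-month visit, so some people missing at 3 months would still contribute information. The 94.1% is therefore a completer-only figure. That does not change how the printed number arises from its stated inputs.
- **2142 may not be a ceiling.** The heading calls it a minimum, and the plan is to invite every eligible patient. The Results section also ties the end of recruitment to the target having completed baseline and a 3-month follow-up. If that means 2142 completers, power is 98.0% and nothing is lost in practice. But that reading conflicts with the sample size section and with the 39% progress figure, and under it the 2142 would no longer contain a 20% allowance.
- **The effect is negligible.** On size this largely stands: 20% is a round planning guess, and 0.9 points of power changes no analysis. It bears on the weight of the point and does not make the printed figure correct.

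**Conclusion.** The concern holds. On the article's own inputs, 2142 at baseline, 20% loss and 95% power cannot all be true together; any two of them fix the third. At 2142 with 95% power the allowable loss is 16.7%. At 2142 with 20% loss the completer power is about 94.1%. At 95% power with 20% loss the baseline number is 2232.

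This rests on two things: reading 0.1 as the standardised mean of the paired change, and, for the cause of the error, an exact numerical match, since the formula is not printed. The study is not materially underpowered. The point deserves correction because a published sample size should follow from its stated assumptions and this one is relied on in several places.

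**What to change.** Restate the sentence in the sample size section and align the abstract. Suggested wording:

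> With a standardised mean change of 0.1 and a two-sided 1% level, 1785 participants with baseline and 3-month data give 95% power. A baseline sample of 2142 allows for 16.7% loss to follow-up; with 20% loss, the power among completers is about 94%.

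Alternatively, keep the 95% power and 20% loss and print 2232 as the baseline number. In either case, say that the 0.1 is scaled to the SD of change, if that is what was meant.

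The first option costs one sentence, a stated power about one point lower at 20% loss, and no extra recruitment. The second raises the stated target by 90.
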